## Abstract

**Introduction:**

The aim of this study is to develop practical and affordable models to (a) diagnose people with diabetes and prediabetes and (b) identify those at risk of diabetes complications so that these models can be applied to the population in low-income and middle-income countries (LMIC) where laboratory tests are unaffordable.

**Methods and analysis:**

This statistical and economic modelling study will be done on at least 48 000 prospectively recruited participants aged 40 years or above through community screening across 20 predefined regions in India. Each participant will be tested for capillary random blood glucose (RBG) and complete a detailed health-related questionnaire. People with known diabetes and all participants with predefined levels of RBG will undergo further tests, including point-of-care (POC) glycated haemoglobin (HbA1c), POC lipid profile and POC urine test for microalbuminuria, retinal photography using non-mydriatic hand-held retinal camera, visual acuity assessment in both eyes and complete quality of life questionnaires. The primary aim of the study is to develop a model and assess its diagnostic performance to predict HbA1c diagnosed diabetes from simple tests that can be applied in resource-limited settings; secondary outcomes include RBG cut-off for definition of prediabetes, diagnostic accuracy of cost-effective risk stratification models for diabetic retinopathy and models for identifying those at risk of complications of diabetes. Diagnostic accuracy inter-tests agreement, statistical and economic modelling will be performed, accounting for clustering effects.

**Ethics and dissemination:**

The Indian Council of Medical Research/Health Ministry Screening Committee (HMSC/2018–0494 dated 17 December 2018 and institutional ethics committees of all the participating institutions approved the study. Results will be published in peer-reviewed journals and will be presented at national and international conferences.

**Trial registration number:**

ISRCTN57962668 V1.0 24/09/2018.

Strengths and limitations of the studyThis is the first national prospective study that will assess the prevalence of sight-threatening diabetic retinopathy (DR) in various regions in India.The study will provide evidence on the accuracy of point-of-care glycated haemoglobin as a screening tool for diabetes.The study will provide several diagnostic models on diabetes and its complications.Validation of the models may not be possible in all cases.The treatment pathway for patients identified with sight-threatening DR or other complications of diabetes is according to local protocols.

## Introduction

### Background

Diabetes and its complications are common causes of morbidity and mortality globally. Low-income and middle-income countries (LMIC) are most affected by the diabetes epidemic, where significant number of people with undiagnosed diabetes present with complications of diabetes.^1^ More than 30% of world population is estimated to have prediabetes.^2^ The most common risk factors for diabetes and its complications are long-term diabetes, uncontrolled hyperglycaemia, hypertension and dyslipidaemia. As high as 90% of people with type 2 diabetes are dyslipidaemic and 60%–85% are hypertensive. In addition, 90% of people with type 2 diabetes are obese.^3^ There is an unmet need to screen for prediabetes and diabetes in LMIC, where primary healthcare is underdeveloped and laboratory tests are costly.

### Screening for people at risk of diabetes

According to the WHO, diabetes is confirmed by laboratory tests in a symptomatic individual if glycated haemoglobin (HbA1c) is ≥48 mmol/L (≥6.5%) or fasting blood glucose is ≥7 mmol/L (≥126 mg/dL), or a random blood glucose (RBG) is ≥11.1 mmol/L (≥200 mg/dL) or after a 2-hour oral glucose tolerance test, blood glucose is ≥11.1 mmol/L (≥200 mg/dL). In asymptomatic individuals, diabetes has to be confirmed by two of these laboratory tests.^4^ Standard laboratory-based HbA1c test has the added advantage of providing an average estimation of the glycaemic status of an individual over the previous 3 months and is helpful in categorising people into normal (HbA1c <42 mmol/mol; <6.0%), prediabetes (HbA1c 42–47 mmol/mol; 6%–6.4%) and diabetes (HbA1c is ≥48 mmol/mol; ≥6.5%).^4^ The lower limit of HbA1c in prediabetes may be as low as 5.7%.^5^

However, none of these tests are practical for population-level screening in LMIC where non-technical personnel often conduct screening for diabetes in non-clinical environments. HbA1c also cannot be measured in patients with haemoglobinopathies. A number of LMIC have high prevalence of malaria and various haemoglobinopathies, including thalassaemia and sickle cell anaemia. Therefore, there is an unmet need to use simple tests to identify people at risk for diabetes. Despite its variability, capillary RBG is the the most common blood test done in such situations.^6^ Prediabetes is not clearly defined by RBG despite several studies that have attempted to define cut-off values of RBG against HbA1c.^6–15^ More convenient point-of-care (POC) HbA1c kits are now available that show good correlation with laboratory-based HbA1c estimation.^16^ It is, therefore, appropriate to validate POC HbA1c against RBG in community screening. Although there are several studies that have evaluated various screening tests for prediabetes, these studies have used laboratory-based HbA1c measurements or fasting blood glucose as the index test.^17^ In contrast, this study will focus on POC HbA1c as the index test for prediabetes to inform community screening. Studies using POC HbA1c as a reference test have included specific disease cohorts only, or had a small sample size within hospital settings or conducted post-hoc analysis on previously recruited study cohorts and most importantly, did not compare the accuracy of these tests with known non-laboratory (NL) based diabetes risk scores.^6–15^

Due to the large numbers of undiagnosed diabetes, it is also useful to investigate whether it is more efficient to triage people at risk of diabetes in the population using non-invasive diabetes risk scores, such as Madras Diabetes Research Foundation-Indian Diabetes Risk Score (MDRF-IDRS)^18^ to further reduce the cost of screening with POC HbA1c or RBG.

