### Objectives

Our study has three important objectives. The first objective is to determine the ideal tests that could identify people at risk of diabetes and prediabetes in community screening that can be applied to LMIC. In order to accomplish this, we would evaluate the correlation of RBG levels with POC HbA1c levels and decide on a cut-off value for RBG from HbA1c to diagnose prediabetes. Second, we will evaluate whether initial triaging with NL diabetes risk score followed by either RBG or POC HbA1c only to the identified risk group is more effective than screening everyone for diabetes using either RBG or POC HbA1c. Third, we will develop affordable, easily deliverable and clinically effective model to accurately identify people at risk of complications of diabetes in community screening, especially DR.

Secondary objectives are aimed at guiding future policies on screening of diabetes and its complications. As the study involves a large sample and the setting up of a teleophthalmology model to screen for DR across 20 regions in India, we will be able to report the regional prevalence of DR and the associated risk factors, the inter-grader reliability and the accuracy of using artificial intelligence to grade DR. We will also conduct economic modelling and process evaluation of a holistic model for screening of all complications of diabetes. If sample size permits, we will be able to report on region-specific and diverse population-specific rates of diabetes and complications, visual impairment, quality of life and risk models specific to regions to inform local health authorities.

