### Stratified sampling

In each region, we predefined a geographic area as urban or rural based on a multistage sampling technique using data from the 2011 census of India. A census enumeration block that usually consists of 125–150 households with a population of 650–700 is the primary sampling unit for urban areas, while villages are defined in the rural areas. Bigger villages are further divided to ensure that approximately 300 households can be covered. The house-to-house survey will be conducted by approaching each household in consecutive streets in each area. If the household members are not available, a further two visits by the fieldworkers are permitted. In each household, all available members aged 40 years or above, who meet the inclusion criteria, will be invited to participate in the study.

The special category groups include two groups: (a) people working under high stress leading to poor and untimely eating habits (such as policemen, truck and taxi drivers, manual labourers, fishermen, factory staff and professionals in stressful jobs) and those presumed to be at low risks such as certain religious groups and (b) people with poor health seeking behaviour and/or under social stigma (such as tribal, slum population and people with infection like HIV or leprosy). All survey clusters and special groups are independent samples. The total population for the study is the total recruited participants in all the 20 regions, including the special population (figure 1).

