### Selection of participants

The inclusion criteria are adults who are ≥40 years of age (special groups may contain adult population of any age), who are local residents of Indian origin and are willing to give informed consent (see online supplemental appendix 1 for sample informed consent form).

10.1136/bmjopen-2020-039657.supp1Supplementary data

Exclusion criteria include vulnerable adults in whom it may not be possible to carry out all the tests; pregnant and breastfeeding women; anyone in the opinion of the fieldworkers deemed too ill to be screened; and those who are currently participating in intervention trials with investigational medicinal products.

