BP will be recorded in sitting position in the right arm to the nearest 1 mm Hg using the electronic OMRON machine (Omron Corporation, Kyoto, Japan). Participants with BP ≥140/90 mm Hg and not on antihypertensive drugs will be advised to contact a physician for further evaluation. A simple finger-prick test will be used to assess capillary RBG using a standard POC testing device (OneTouch Verio Glucometer, LifeScan Inc, USA). All participants with known diabetes or those with capillary RBG ≥160 mg/dL and 50 participants with RBG 110–159 mg/dL in each cluster will receive further tests. These include HbA1c estimation using a POC kit (A1c Now Plus, PTS Diagnostics, USA) and POC lipid estimation (Cardiochek PA analyser, PTS Diagnostics, USA). A POC urine sample (Chemstrip Micral dipstick, Roche Diagnostics, Mannheim) will be tested for the presence or absence of microalbuminuria.

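### POC HbA1c anchors the RBG cut-off, the primary aim and the primary outcome, yet people with a known haemoglobinopathy, in whom the protocol says HbA1c cannot be measured, are not set aside

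*Protocol article*

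**What the plan says.** In the Introduction, under Screening for people at risk of diabetes, the protocol article says that "HbA1c also cannot be measured in patients with haemoglobinopathies". It continues: "A number of LMIC have high prevalence of malaria and various haemoglobinopathies, including thalassaemia and sickle cell anaemia". The next sentence draws the design conclusion: "Therefore, there is an unmet need to use simple tests to identify people at risk for diabetes".

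HbA1c is then used as the anchor in four places:

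- Objectives: the study will "decide on a cut-off value for RBG from HbA1c to diagnose prediabetes".
- Abstract, Methods and analysis: the primary aim is to "develop a model and assess its diagnostic performance to predict HbA1c diagnosed diabetes from simple tests".
- Statistical considerations, Table 1: POC HbA1c is the reference standard in the prediabetes row, with RBG and the risk scores as index tests.
- Outcomes: the primary outcome is the correlation between RBG and POC HbA1c.

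Study procedures sends three groups to second-stage testing: all participants with known diabetes, all with RBG of at least 160 mg/dL, and 50 per cluster with RBG of 110 to 159 mg/dL. Of the further tests it says "These include HbA1c estimation using a POC kit", and no exception is stated. Selection of participants lists the exclusions: vulnerable adults who may be unable to do all the tests, pregnancy or breastfeeding, being too ill in the fieldworker's opinion, and current participation in a drug trial. None concerns haemoglobinopathy. The list of strengths and limitations does not mention it either.

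**The concern.** The article names a group in which its own anchor measurement fails, uses that failure as part of the argument for RBG, and then ties RBG to that measurement without setting the group aside. If an affected person's POC HbA1c returns a number, that number enters the correlation, the cut-off and the accuracy estimates as though it were valid. If it returns nothing, the person is lost from the derivation, and the resulting cut-off is then offered for screening populations that include such people. Either way, the cut-off has not been validly established in a group that the rationale specifically mentions.

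**Working it through.** The point is a comparison of printed statements; the only arithmetic is on denominators.

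**1. Rationale against reference.** The Introduction treats HbA1c as unusable in haemoglobinopathy. Objectives, Table 1 (prediabetes row), the abstract's primary aim and Outcomes all need a usable HbA1c from each tested participant. Both can hold only if affected participants are identified and handled separately.

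**2. Is there a printed filter?** Three places could hold one.

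- Selection of participants: no criterion on haemoglobinopathy. The clause that reads "Exclusion criteria include vulnerable adults in whom it may not be possible to carry out all the tests" concerns whether tests can be carried out in vulnerable adults, not whether a result is valid.
- Study procedures: the second-stage rule depends only on known diabetes and RBG level.
- Statistical considerations: no alternative reference and no rule for an unobtainable or unreliable HbA1c.

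**3. How many HbA1c results are in play?** Inputs: 20 regions and 3 clusters per region (Study setting), 50 per cluster in the middle RBG band (Study procedures), and 4800 known plus 4800 newly detected diabetes (Sample size calculation).

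- Middle band: 20 × 3 × 50 = 3000.
- All second-stage tests: 4800 + 4800 + 3000 = 12,600. This is approximate, because the article does not say how many people will have RBG of at least 160 mg/dL.

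**4. What does an affected fraction mean?** The documents give no prevalence, so this is scaling and not an estimate. Each percentage point of affected participants corresponds to 0.01 × 3000 = 30 results in the middle band and 0.01 × 12,600 = 126 overall. An assumed range of 1% to 10% therefore spans 30 to 300 and 126 to 1260.

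**5. What could that do to the primary outcome?** For illustration, suppose a fraction h of tested people have HbA1c values unrelated to RBG but with the same mean and variance as everyone else. The observed correlation is then (1 − h) × r. With h = 1% it is 0.99r; with h = 10% it is 0.90r. Other assumptions give other answers: a systematic shift in HbA1c would move the cut-off in a direction set by the shift, and missing values would only remove pairs. The documents do not say which applies.

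**6. The plan's own sample-size figures** do not bear on this point. They reproduce: 4800 × 0.30 + 4800 × 0.15 = 2160 with retinopathy, of whom 216 (10%) are expected to be sight-threatening.

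**The case against.** The strongest reply is that this is a condensed article. Study procedures collects a brief medical history on a case report form that is not shown, and Statistical considerations defers methods to an analysis plan that is also not shown; either might record haemoglobinopathy or deal with unusable results. That is fair as far as it goes, and nothing here asserts that those documents are silent. But the eligibility criteria, the testing rule and the choice of reference are all printed, and as printed they conflict with the Introduction.

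A second reply is that the study also sets out to assess POC HbA1c as a screening tool, so unselected field performance is a reasonable target. That defends reporting results with everyone included. It does not defend using those values alone to set the RBG cut-off.

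A reader might infer something stronger in four ways, and the documents do not support them.

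- *HbA1c is the truth throughout.* Table 1 makes RBG the reference in the diabetes row. The point is confined to the prediabetes cut-off, the abstract's primary aim and the primary outcome, and to people given second-stage tests rather than all 48,000.
- *The values are wrong.* The Introduction says that HbA1c cannot be measured, which may mean missing rather than erroneous results. Missing pairs would be a lesser problem.
- *RBG is mainly for people with haemoglobinopathies.* Cost and practicality are the main rationale; haemoglobinopathy is an additional one.
- *Cases cluster in the special strata.* Stratified sampling gives examples "such as tribal, slum population and people with infection like HIV or leprosy", but nothing in the article links any of these groups to haemoglobinopathy. A count for those strata, or a predicted false difference in accuracy between strata, has no basis in the documents.

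**Conclusion.** The inconsistency stands, within limits. Known haemoglobinopathy is a stated ground for not using HbA1c, and the printed rules still let affected participants into, or lose them silently from, the analyses anchored on POC HbA1c. The size and direction of any bias cannot be derived: no prevalence is given, the failure may be missingness or error, and an analysis plan or case report form not shown could already cover part of it. Only a subgroup of those tested is affected, so the RBG calibration as a whole is not invalidated. The change is worth making because it is cheap and removes a contradiction in the stated rationale, not because a large effect has been shown.

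**What to change.** 1. Add one item on known haemoglobinopathy to the medical history. Study procedures already plans to refine the case report form after validating the questionnaires in 200 subjects.
2. Exclude participants who report one from the HbA1c-referenced analyses: the RBG–HbA1c correlation, the RBG cut-off, and accuracy for HbA1c-diagnosed diabetes or prediabetes. Keep them in the retinopathy models.
3. Report those analyses with and without these participants, and give the number of HbA1c results that could not be obtained.
4. List undiagnosed haemoglobinopathy as a limitation.

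The cost is one question, one additional set of reported estimates and slightly fewer HbA1c pairs. Self-report removes known cases only; undiagnosed carriers remain, which is why the fourth step is needed.

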### Screening for complications of diabetes mellitus

Approximately 30% of people with diabetes present with macrovascular complications such as cardiovascular, cerebrovascular and peripheral vascular diseases.^3^ In addition, this population may also have microvascular complications, including diabetic kidney disease (DKD) in 30%–50%, diabetic retinopathy (DR) in 30% and diabetic neuropathy in 30%–50%.^3^ Despite this public health burden, people with diabetes are not systematically screened for these complications of diabetes in LMIC due to economic constraints, paucity of public health programmes, inadequately trained manpower and under-resourced infrastructure. Recently, several cardiovascular risk scores such as the NL INTERHEART risk score (IHRS) have been successfully used in community screening programmes.^19^ It may be possible to develop similar models to identify people at risk of sight-threatening DR (STDR) and blindness. Although systematic annual photographic retinal screening after pupil dilatation using standard costly retinal cameras and prompt treatment of STDR have reduced the rate of blindness in the UK,^20^ these complex and costly screening protocols are not translatable to LMIC and hence alternative screening methods must be considered to ensure population coverage. There are recent reports of accuracy of identifying STDR from the retinal images obtained by affordable and portable non-mydriatic cameras and graded either manually or by artificial intelligence.^21 22^ Therefore, adding retinopathy screening, using these hand-held retinal cameras, to minimally invasive tests, such as blood pressure (BP) and urine dip test for microalbuminuria and other NL risk scores, may be an efficient and cost-effective screening option to identify people at risk of diabetes complications.

### Objectives

Our study has three important objectives. The first objective is to determine the ideal tests that could identify people at risk of diabetes and prediabetes in community screening that can be applied to LMIC. In order to accomplish this, we would evaluate the correlation of RBG levels with POC HbA1c levels and decide on a cut-off value for RBG from HbA1c to diagnose prediabetes. Second, we will evaluate whether initial triaging with NL diabetes risk score followed by either RBG or POC HbA1c only to the identified risk group is more effective than screening everyone for diabetes using either RBG or POC HbA1c. Third, we will develop affordable, easily deliverable and clinically effective model to accurately identify people at risk of complications of diabetes in community screening, especially DR.

Secondary objectives are aimed at guiding future policies on screening of diabetes and its complications. As the study involves a large sample and the setting up of a teleophthalmology model to screen for DR across 20 regions in India, we will be able to report the regional prevalence of DR and the associated risk factors, the inter-grader reliability and the accuracy of using artificial intelligence to grade DR. We will also conduct economic modelling and process evaluation of a holistic model for screening of all complications of diabetes. If sample size permits, we will be able to report on region-specific and diverse population-specific rates of diabetes and complications, visual impairment, quality of life and risk models specific to regions to inform local health authorities.

## Methods and analysis

### Study design

This is a statistical and economic modelling study that will be done on cross-sectional and prospectively recruited participants from community-based screening in order to accurately identify people at risk of diabetes, prediabetes and complications of diabetes.

### Study setting

This community screening will be conducted across 20 regions in India, each led by a local clinical centre with a trained ophthalmologist responsible for the study at that site (figure 1). Each region will have three clusters stratified into urban, rural and a predefined special category of population such as people with poor access to healthcare, or persons that are presumed to be at high risk or low risk of developing diabetes. The study will involve a door-to-door survey, with questionnaires and POC tests performed by fieldworkers. Each cluster will screen at least 800 consenting individuals aged 40 years or above for a cumulative sample size of a minimum of 48 000 participants. If any cluster or centre does not reach their target recruitment, it will be made up by another cluster or centre with the same stratified population.

